## 7.1 ZD6474 DOSE MODIFICATIONS

For guidance on the management of QTc prolongation, see Figure 1 below. For all other toxicities, the dose of study treatment will be withheld for up to 3 weeks until the toxicity has resolved to CTCAE grade 1 or better, and then study treatment may be restarted. Patients will be withdrawn from the study if toxicity does not resolve to CTCAE grade 1 or better within 3 weeks. Dose reduction/re-challenge for each toxicity criterion will be managed as discussed in the sections that follow.

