### 3.2 DOSE LIMITING TOXICITIES

DLTs (defined as within the first 28 days of treatment in dose level 1 and first 35 days in dose levels 2-4) will include: grade IV hematological toxicity > 7 days; fever and neutropenia; grade III diarrhea leading to hospitalization or lasting > 48 hours despite aggressive anti-diarrheal medication; grade IV diarrhea despite aggressive anti-diarrheal medication; grade IV vomiting despite optimal antiemetics; or grade III or higher nonhematological toxicity (excluding nausea, vomiting, diarrhea, or alopecia) lasting > 1 week; grade 4 skin toxicity; grade 3 or greater cardiac toxicities; or death.

If patients in dose levels 2-4 who have a DLT in the first 14 days (prior to initiation of irinotecan), the patient will not be counted towards the DLTs of that cohort and an additional patient will be substituted. For example, if one of the first 3 patients in dose level 2 have a DLT, that patient will not be calculated into the DLT tabulation for ZD6474, cetuximab and irinotecan and an additional patient will be substitute in that spot. If this scenario occurs twice, the study will be held and the study team will reevaluate the ZD6474 / cetuximab toxicities.

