### 3.5 DURATION OF THERAPY

Patients will continue the study treatment until disease progression, unacceptable toxicity, or development of any of the criteria for patient discontinuation as described in Section 11 of the protocol.

Patients will be considered to be on-study for the duration of their treatment and during the 30 days following treatment discontinuation. Treatment discontinuation is defined as the last day of study treatment.

All included patients will be followed up until recovery or stabilization of all adverse events or return to baseline condition.

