## 4 STUDY POPULATION

### 4.1 INCLUSION CRITERIA

Patients must meet all of the following criteria in order to be eligible for entry into the trial:

- (1) Eligible patients must have histologically or cytologically documented locally advanced or metastatic colorectal cancer
- (2) 1-2 prior therapies for metastatic colorectal cancer. Prior adjuvant therapy not included in the number of priors unless recurrence within 12 months of last dose of therapy and then the adjuvant therapy will be counted as 1 prior.
- (3) Patients must have measurable disease according to the RECIST criteria.
- (4) Tumor is K-ras wildtype by method of choice at respective institution (testing codons 12 and 13). Since testing for K-ras should be standard of care for use of cetuximab in metastatic colorectal cancer, testing can be performed prior to signing consent or after consent but prior to enrollment.
- (5) Age > 18 years
- (6) ECOG Performance Score of 0-2.
- (7) Patients should have completed any major surgery 4 weeks from registration. Patients must have completed any minor surgery 2 weeks from registration. Patients must have fully recovered from the procedure and have completely healed surgical incisions before starting therapy.. (Insertion of a vascular access device is not considered major or minor surgery.)
- (8) Adequate bone marrow as evidenced by:
  - Absolute neutrophil count  $\geq 1,200/\text{mL}$
  - Platelet count  $\geq 100,000/\text{mL}$
- (9) Adequate renal function as evidenced by serum creatinine  $\leq 1.5 \times \text{ULRR}$  or creatinine clearance  $\geq 50 \text{ mL/minute}$  (calculated by Cockcroft-Gault formula)
- (10) Adequate hepatic function as evidenced by:
  - Serum total bilirubin  $\leq 1.5 \text{ mg/dL}$
  - Alkaline phosphatase  $< 3\text{X}$  the ULN for the reference lab ( $< 5\text{X}$  the ULN for patients with known hepatic metastases)
  - SGOT/SGPT  $< 3\text{X}$  the ULN for the reference lab ( $< 5\text{X}$  the ULN for patients with known hepatic metastases)
- (11) Normal range of serum calcium (ionized or adjusted for albumin) and magnesium (supplementation permitted)
- (12) Patients or their legal representatives must be able to read, understand and provide informed consent to participate in the trial.

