### 7.1.3 Management of Patients With QTc Prolongation

For a single QTc value of  $\geq 550$  msec or an increase of  $\geq 100$  msec from baseline, ZD6474 must be withheld. ECGs and electrolytes should be followed 3 times a week until QTc falls below 480 msec or baseline, whichever is higher. ZD6474 treatment may be resumed at a lower dose after the QTc recovers to  $< 480$  msec or baseline. For a QTc interval  $\geq 500$  msec, but  $< 550$  msec, or an increase of  $\geq 60$  msec but  $< 100$  msec from baseline QTc to a QTc value  $\geq 480$  msec, ZD6474 may be continued but a repeat ECG (in triplicate) must be obtained within 48 hours. If QTc prolongation is confirmed, ZD6474 should be withheld. ECGs and electrolytes should be checked 3 times a week until QTc falls below 480 msec or baseline, whichever is higher. ZD6474 treatment may be resumed at a lower dose, as outlined in section 7.1.1 after the QTc recovers to  $< 480$  msec or baseline. If the patient does not meet the criteria for QTc prolongation at the repeat ECG, then the patient should continue treatment and resume the ECG schedule as outlined in the Study Plan.

If ZD6474 is restarted after the QTc prolongation has resolved, ECGs should be performed 1, 2, 4, 8, 12 weeks and then every 3 months after treatment is restarted. If ZD6474 must be withheld for  $> 3$  weeks to allow for QTc prolongation to recover to  $< 480$  msec or baseline, the patient will be withdrawn from study. If QTc prolongation recurs after the dose reduction as detailed, the patient must permanently discontinue treatment with study medication.

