#### 7.1.6 Management of Other Toxicity

If any other grade 3 or 4 toxicity that is not outlined elsewhere in Sections 7.1 develops and is deemed attributable to ZD6474, ZD6474 should be withheld until the toxicity resolves to grade 1 or below. Upon recovery, treatment may resume at a permanent reduced dose. If ZD6474 must be withheld for more than 3 weeks for resolution of toxicity, the patient will be withdrawn from study.

Patients who develop CTCAE grade 3 hypertension may continue on therapy if blood pressure is controlled on antihypertensive medication. If blood pressure cannot be stabilized with increased antihypertensive medication, study treatment must be discontinued and cannot be resumed until blood pressure is controlled to baseline level. Patients with CTCAE grade 4 hypertension should discontinue study treatment and cannot resume therapy until blood pressure is controlled to baseline level. If study treatment must be interrupted for more than 3 weeks to allow for toxicity to resolve, the patient's study participation will be discontinued.

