### 7.3 Irinotecan Dose Reductions

Treatment with irinotecan can resume if  $ANC \geq 1200/mm^3$ , the platelet count is  $\geq 100,000/mm^3$ , and any other irinotecan-related toxicity resolved to  $\leq$  grade 1. If irinotecan is held for irinotecan-related toxicities that are not attributable to ZD6474 or cetuximab, treatment with cetuximab and ZD6474 may continue. **Irinotecan cannot be delayed for more than 3 weeks or the patient should be removed from protocol therapy.**

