## 9.2 Evaluation during treatment

Clinical examination including a complete physical examination, ECOG PS, vital signs, hematology, biochemistries, toxicity assessment and documentation of concomitant medications will be performed as noted in below required data table (Section 10). Toxicity will be assessed according to the NCI CTCAE V 3.0.

Initial tumor response will be assessed every 8 weeks and tumor assessment should be repeated no sooner than 4 weeks after a response for confirmation.

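### The ZD6474 recovery rule and the DLT definition ignore the raised liver tests that inclusion criterion 10 allows at entry

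*Protocol*

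**What the plan says.** **Entry.** Section 4.1, inclusion criterion 10, sets the limit for alkaline phosphatase and for SGOT/SGPT at below 3 times the ULN, widened to below 5 times "the ULN for patients with known hepatic metastases". Exclusion 22 in Section 4.2 removes patients with more than grade 1 toxicity left from earlier anti-cancer therapy. It does not cover liver tests raised by metastases.

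**Grading.** Section 9.2: "Toxicity will be assessed according to the NCI CTCAE V 3.0". The liver-test cut points are not printed.

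**Recovery.** Section 7.1, for everything except QTc: "Patients will be withdrawn from the study if toxicity does not resolve to CTCAE grade 1 or better within 3 weeks". Section 7.1.1 repeats this. Section 7.1.6 covers other grade 3 or 4 toxicity that is "deemed attributable to ZD6474, ZD6474 should be withheld until the toxicity resolves to grade 1 or below", and the summary table in 7.1.7 agrees.

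**DLT.** Section 3.2, repeated in the synopsis and in Section 7, counts "grade III or higher nonhematological toxicity (excluding nausea, vomiting, diarrhea, or alopecia) lasting > 1 week". It does not mention the entry value or attribution to treatment.

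**Where baseline is used.** Under Section 7.1.3, ECGs and electrolytes are followed "until QTc falls below 480 msec or baseline, whichever is higher". Section 7.1.6 ties resumption after uncontrolled or grade 4 hypertension to the baseline blood pressure. Section 3.5 says patients are "followed up until recovery or stabilization of all adverse events or return to baseline condition", but that governs length of follow-up, not resumption or withdrawal.

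**The concern.** Criterion 10 deliberately admits patients whose liver tests are raised by their disease, yet the later rules judge those tests on an absolute scale.

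Two things are at stake. First, an eligible patient could lose study treatment although the liver test is back where it stood at entry, which would also curtail that patient's contribution to the secondary efficacy endpoints. Second, a small movement from a high entry value could be scored as a DLT. Under Section 3.1 the decision at each dose level turns on whether 0, 1 or 2 patients out of 3 to 6 have a DLT, so a single event of doubtful meaning can change the MTD, which is the primary objective.

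**Working it through.** **1. The plan's own table.** With p the DLT probability per patient, the escalation rule in Section 3.1 gives

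P(too toxic) = 1 − [(1−p)³ + 3p(1−p)²(1−p)³].

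At p = 0.20: 1 − [0.512 + 0.197] = 0.291. At 0.30, 0.40, 0.50 and 0.60 the results are 0.506, 0.691, 0.828 and 0.918. All five values in Section 13 (0.29, 0.51, 0.69, 0.83, 0.92) reproduce, so the table is not in question.

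**2. Recovery rule against entry limit.** Let c be the top of grade 1, in multiples of ULN, and b the entry value. Returning to b fails Section 7.1 whenever b > c. Criterion 10 allows b < 3, or b < 5 with hepatic metastases. The value of c is assumed:

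| Assumed c | Entry values that cannot meet the rule by returning to baseline |
|---|---|
| 2.5 | above 2.5 and below 3; with hepatic metastases, above 2.5 and below 5 |
| 3 | only with hepatic metastases, above 3 and below 5 |
| 5 | none |

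The conflict needs no model of laboratory variation, only c below a permitted entry value.

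**3. Rise needed to reach grade 3.** Let g be the assumed start of grade 3. The rise needed is g/b − 1.

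| Entry value b | g = 5 | g = 8 | g = 10 |
|---|---|---|---|
| 4.5 x ULN | 11% | 78% | 122% |
| 4.0 x ULN | 25% | 100% | 150% |
| 3.0 x ULN | 67% | 167% | 233% |

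The rise counts only if it lasts more than a week within the DLT window (28 days at level 1, 35 days at levels 2-4). It is a small rise only when g is close to 5 and b is close to the entry limit.

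**4. Can the effect on the MTD be computed?** Suppose a share f of patients enters with raised tests and each has a chance r of a spurious DLT, independent of true DLTs. Then p becomes q = 1 − (1−p)(1−fr). For illustration only, at p = 0.20:

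- f = 10%, r = 10%: q = 0.208, P(too toxic) = 0.31.
- f = 30%, r = 50%: q = 0.32, P(too toxic) = 0.55.

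The protocol gives neither f nor r, and the answer runs from almost no change to a large one. No figure for the MTD effect can be defended.

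**The case against.** **Section 7 is not triggered by entry status.** A reader might infer that anyone entering above grade 1 must be withdrawn. The text does not support that: the Section 7 guidelines apply only after a DLT or a treatment-related toxicity, and 7.1.6 requires grade 3 or 4 attributed to ZD6474. This stands and narrows the point to patients who have had such an event.

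**A value back at entry is no longer a toxicity.** Section 8.2 defines an adverse event as a new or worsened condition, so a return to the entry value could be read as resolution. That reading is reasonable but not what Section 7.1 says. It names a grade, and the same section writes baseline into the QTc and hypertension rules where that was meant.

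**Irinotecan.** A reader might extend the withdrawal problem to irinotecan, because Section 7.3 lets treatment resume only with "any other irinotecan-related toxicity resolved to" grade 1 or lower. The table in 7.3.5 holds irinotecan for other grade 3/4 toxicity only until grade 2 or lower, so a patient back at an entry grade 2 could resume. The two passages contradict each other, and the withdrawal consequence is not established for irinotecan.

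**The DLT count has other filters.** At levels 2-4, a DLT in the first 14 days leads to replacement and is not counted, although a second such case puts the study on hold. Section 8.2 says signs of disease progression are not adverse events, which may remove some rises, although the DLT definition does not refer to it. Two weekly draws seven days apart do not by themselves show more than a week. These limits stand and reduce the frequency of spurious DLTs without closing the gap.

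**A conservative choice.** Counting every grade 3 event regardless of cause is a defensible cautious design. The difficulty is that it sits unexplained beside an entry criterion that admits values possibly just below the line.

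**Conclusion.** The concern holds in a limited form. For ZD6474, the recovery wording in Sections 7.1, 7.1.1, 7.1.6 and 7.1.7 conflicts with inclusion criterion 10 for patients who enter above the grade 1 ceiling and later have a qualifying toxicity: read literally, full return to the entry value still leads to withdrawal. This rests on one assumption, that grade 1 ends below a permitted entry value.

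The DLT part is more conditional. It matters if grade 3 begins near 5 x ULN, where rises of 11% from 4.5 x or 25% from 4.0 x, sustained for more than a week, would count. It largely vanishes at 8 to 10 x ULN.

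A reader might infer that the MTD is biased downwards by a known amount, or that this trial's MTD was in fact affected. The protocol supports neither: it does not give the share of patients near the limit, the size of week-to-week variation or any DLT data. The point merits correction, but it does not undermine the escalation design or the table in Section 13.

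**What to change.** 1. Reconcile the ZD6474 recovery wording (7.1, 7.1.1, 7.1.6 and the 7.1.7 table) and the DLT definition (synopsis, 3.2 and 7) with inclusion criterion 10. The clinical team decides how; no threshold or criterion is proposed here.
2. Separately, reconcile Section 7.3 (grade 1) with the 7.3.5 table (grade 2) for irinotecan.
3. In the analysis, list entry values for patients with raised liver tests, stating what counts as raised. Show the DLT tally by dose level with and without liver-test events in those patients.

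**Cost.** A short amendment, one more comparison when DLTs are adjudicated and one extra table. Liver tests are already collected at screening (Section 10). The protocol's alert page records closure to accrual in May 2010, so new wording cannot change the escalation decisions already taken. It would serve any patients still on treatment, and the reporting in item 3 is useful regardless.

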### 7.1.1 Dose reduction table

Patients will be withdrawn from the study if toxicity does not resolve to  $\leq$  CTCAE grade 1 within 3 weeks. Dose reduction will be dependent on the original dose. A guideline for dose reduction is shown in the table below. There will be no dose reescalations for an individual patient (ie. dose reductions for ZD6474 will be permanent).

| Current dose | Reduced dose                     | ZD6474 dispensed for reduced dose | Tablets per daily dose |
|--------------|----------------------------------|-----------------------------------|------------------------|
| 300 mg       | 200 mg                           | 100-mg ZD6474 tablets             | 2                      |
| 200 mg       | 100 mg                           | 100-mg ZD6474 tablets             | 1                      |
| 100 mg       | 100 mg
every other day |                                   | 1 every other day      |

### 7.1.2 QTc PROLONGATION

Patients will have ECGs performed to monitor QTc interval (using Bazett's correction) as outlined in the study plan.

Figure 1 Flowchart detailing management of QTc prolongation

Figure 2 Flowchart detailing management of QTc prolongation

[figure not shown]

For this study, QTc prolongation is defined as:

(1) A single QTc value of  $\geq 550$  msec or an increase of  $\geq 100$  msec from baseline

**OR**

(2) Two consecutive ECG measurements, within 48 hours of one another, in which either of the following criteria are met for both QTc values (the second being the mean of 3 consecutive ECGs):

- A QTc interval  $\geq 500$  msec but  $< 550$  msec **OR**
- An increase of  $\geq 60$  msec, but  $< 100$  msec, from baseline QTc to a QTc value  $\geq 480$  msec.

Use baseline QTc as noted in the Required Data Table (Section 10, ‡)

### 7.1.3 Management of Patients With QTc Prolongation

For a single QTc value of  $\geq 550$  msec or an increase of  $\geq 100$  msec from baseline, ZD6474 must be withheld. ECGs and electrolytes should be followed 3 times a week until QTc falls below 480 msec or baseline, whichever is higher. ZD6474 treatment may be resumed at a lower dose after the QTc recovers to  $< 480$  msec or baseline. For a QTc interval  $\geq 500$  msec, but  $< 550$  msec, or an increase of  $\geq 60$  msec but  $< 100$  msec from baseline QTc to a QTc value  $\geq 480$  msec, ZD6474 may be continued but a repeat ECG (in triplicate) must be obtained within 48 hours. If QTc prolongation is confirmed, ZD6474 should be withheld. ECGs and electrolytes should be checked 3 times a week until QTc falls below 480 msec or baseline, whichever is higher. ZD6474 treatment may be resumed at a lower dose, as outlined in section 7.1.1 after the QTc recovers to  $< 480$  msec or baseline. If the patient does not meet the criteria for QTc prolongation at the repeat ECG, then the patient should continue treatment and resume the ECG schedule as outlined in the Study Plan.

If ZD6474 is restarted after the QTc prolongation has resolved, ECGs should be performed 1, 2, 4, 8, 12 weeks and then every 3 months after treatment is restarted. If ZD6474 must be withheld for  $> 3$  weeks to allow for QTc prolongation to recover to  $< 480$  msec or baseline, the patient will be withdrawn from study. If QTc prolongation recurs after the dose reduction as detailed, the patient must permanently discontinue treatment with study medication.

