- (14) QTc with Bazett's correction that is unmeasurable, or  $\geq 480$  msec on screening ECG. If a patient has QTc  $\geq 480$  msec on screening ECG, the screen ECG may be repeated twice. The average QTc from the three screening ECGs must be  $< 480$  msec in order for the patient to be eligible for the study.) Patients who are receiving a drug that has a risk of inducing

Torsades de Pointes are excluded if QTc is  $\geq 460$  msec (see Appendix A, Drug List 1; section 5.2)

- (15) Any concomitant medication that are potent inducers of CYP3A4 (rifampicin, rifabutin, phenytoin, carbamazepine, Phenobarbital, St. John's Wort) For a comprehensive list of medications which may affect activity of CYP3A4, please visit:

<http://www.medicine.iupui.edu/clinpharm/ddis/ClinicalTable.asp> and  
<http://www.pharmacytimes.com/issue/pharmacy/2008/2008-09/2008-09-8687>.

- (16) Hypertension not controlled by medical therapy (systolic blood pressure greater than 160 mm Hg or diastolic blood pressure greater than 100 mm Hg)
- (17) Patients lacking physical integrity of the upper gastrointestinal tract or who have malabsorption syndrome.
- (18) Currently active diarrhea that may affect patient's ability to absorb ZD6474 or tolerate potential diarrhea from study drugs.
- (19) Receipt of any investigational agents within 30 days prior to commencing study treatment
- (20) Last dose of prior chemotherapy or radiation therapy discontinued less than 4 weeks before the start of study therapy
- (21) Incompletely healed surgical incisions, at the discretion of the investigator.
- (22) Any unresolved toxicity greater than CTC grade 1 from previous anti-cancer therapy
- (23) EGFR by immunohistochemistry will NOT be an exclusion

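### Protocol Sections 7.1.2, 7.1.3 and 7.1.7 disagree on when a QTc prolongation is over: for baselines below 380 msec, one ECG value can be both prolonged and recovered

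*Protocol*

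**What the plan says.** **Definition (Protocol Section 7.1.2).** The criteria follow the words "For this study, QTc prolongation is defined as". The first is "A single QTc value of $\geq 550$ msec or an increase of $\geq 100$ msec from baseline". It needs no confirmation, and its increase part has no minimum absolute QTc. The second needs two measurements within 48 hours. It is met by a QTc of 500 to below 550 msec, or by a rise of 60 to below 100 msec that ends at a stated floor: "msec, from baseline QTc to a QTc value $\geq 480$ msec".

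**Action (Section 7.1.3).** When the first criterion is met, the instruction is "msec from baseline, ZD6474 must be withheld". ECGs and electrolytes are then followed three times a week "until QTc falls below 480 msec or baseline, whichever is higher". The restart sentence begins "ZD6474 treatment may be resumed at a lower dose after the QTc recovers to" and goes on to name below 480 msec or baseline, without the higher-of-the-two qualifier. The sentence that withdraws a patient held for more than three weeks omits the qualifier too. Finally: "If QTc prolongation recurs after the dose reduction as detailed, the patient must permanently discontinue treatment with study medication".

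**Summary table (Section 7.1.7).** Recovery is again 480 msec or baseline, with no qualifier. The second QTc row lists a rise of 60 msec or more and omits the 480 msec floor.

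**Baseline.** Section 4.2, criterion 14, limits the screening value: where the screening ECG is repeated, "The average QTc from the three screening ECGs must be" below 480 msec. A 460 msec limit applies to patients on Torsades-risk drugs. Section 10 defines baseline separately, as the mean of at least three consecutive pre-dose ECGs, and states no upper limit for it.

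**The concern.** One prolongation criterion is a change from baseline. The recovery wording names an absolute limit and the baseline side by side, and only the monitoring sentence says how to choose between them. A site therefore cannot tell from the text when an event opened by a rise of 100 msec has closed.

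Two sites could treat the same patient in opposite ways. One could restart at once at a permanently reduced dose while QTc is still 100 msec or more above baseline, and then stop treatment permanently on an unchanged value. The other could hold the drug until QTc is back at baseline and withdraw the patient after three weeks. The synopsis expects three centers.

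QTc prolongation is a recognised effect of ZD6474 (Section 1.7). Section 6.1 reports 12 confirmed cases in Study ZD6474IL/0003, 6 of them in the first 28 days. QTc-driven reductions and discontinuations will be part of any description of tolerability, so they should mean the same thing at every site.

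**Working it through.** The protocol states no computed figure on this point, so there is none to reproduce. Let B be the baseline QTc and Q the on-treatment QTc, both in msec.

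**Step 1. The rules as inequalities.**
- Prolonged, first criterion, increase part (Section 7.1.2): Q − B ≥ 100.
- Recovered, reading A (higher of the two): Q < max(480, B), which is Q < 480 for any B below 480.
- Recovered, reading B (return to baseline): Q must come back to B.

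**Step 2. Overlap under reading A.** Both hold when B + 100 ≤ Q < 480, which requires B < 380.

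| Baseline | Q both prolonged and recovered |
|---|---|
| 350 | 450–479 |
| 360 | 460–479 |
| 370 | 470–479 |
| 379 | 479 only |
| 380 or more (below 480) | none |

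**Step 3. One patient traced.** B = 370 and Q = 475, a rise of 105.
- Reading A: the drug must be withheld (105 ≥ 100), but 475 < 480, so the monitoring endpoint and the restart condition are met on the same ECG. After restart at the lower dose, a QTc still at 475 again meets the first criterion. It can be read as a recurrence, which means permanent discontinuation.
- Reading B: 475 is 105 above 370, so the hold continues. If QTc has not returned to 370 within three weeks, the patient is withdrawn.

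**Step 4. The other criteria in Section 7.1.2.** Values of 550 or more, and of 500 to below 550, lie above 480. A rise of 60 to below 100 counts only at 480 or more. Enumerating whole-msec baselines from 320 to 479 finds no overlap for any of these. The overlap belongs to the 100 msec rise alone, the only one of these criteria that can be met below 480.

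**Step 5. Section 7.1.7 table.** With the floor omitted, the overlap is B + 60 ≤ Q < 480, so B < 420. At B = 400 it is 460–479.

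**Step 6. Reading B.** Q cannot be at or below B and also at least 100 above it, so there is no overlap. The two readings differ in consequence, as Step 3 shows.

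**Step 7. Size.** The documents give no baseline distribution. Assume normal baselines with mean m and SD s, so the share below 380 is Φ((380 − m)/s). The last column multiplies by the maximum enrolment of 34 (Section 3.3).

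| m, s | (380 − m)/s | Share below 380 | Of 34 |
|---|---|---|---|
| 400, 25 | −0.80 | 21.2% | 7.2 |
| 410, 20 | −1.50 | 6.7% | 2.3 |
| 420, 20 | −2.00 | 2.3% | 0.8 |
| 430, 15 | −3.33 | 0.04% | 0.01 |

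For the table version, the share below 420 runs from about 25% (m = 430, s = 15) to 91% (m = 400, s = 15). These are shares of patients whose baseline makes the conflict possible. They are not event rates.

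**Step 8. Rough number affected under Section 7.1.2.** The Part A percentages in Section 1.8 fit about 83 patients on ZD6474 (46/83 = 55.4%, 30/83 = 36.1%). Taking the 12 confirmed cases over that inferred denominator, 12/83 = 14%, and 0.145 × 34 ≈ 4.9 patients. Suppose all of them had rises of 100 msec or more, with the excess over 100 exponential (mean 10 to 20 msec) and baselines normal (mean 400 to 420, SD 20 to 25 msec). Then 0.6% to 13% of events start below 480, and 4.9 × 0.006 to 4.9 × 0.13 gives about 0.03 to 0.6 patients.

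**The case against.** The best defence is textual. The higher-of-the-two qualifier governs only how long monitoring lasts. Section 7.1.3 also speaks of restarting once the prolongation has resolved, and a patient still 105 msec above baseline has arguably not resolved. An unchanged value is more naturally persistence than recurrence. The management flowchart, to which Section 7.1 refers, is not reproduced in the text at hand and may settle the matter. An absolute restart limit can also be a deliberate choice. These points soften the conflict. They do not remove it, because the restart sentence still offers two thresholds and does not say which applies.

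A reader might infer three stronger things that the documents do not support.
- **That the recovery rule ignores baseline, or that its baseline clause does nothing.** Baseline is named. Under the higher-of-the-two wording, a baseline below 480 does not govern. But the 480 limit applies to the screening value, and the separately measured baseline has no stated cap, so the clause would operate at or above 480.
- **That the hold is empty.** ZD6474 must still be withheld, and it may resume only at a lower dose.
- **That the MTD is distorted.** Section 3.2 defines DLTs by grade, duration and type of event and does not use the Section 7.1.2 or 7.1.3 criteria. No effect on the DLT count is shown.

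**Conclusion.** The inconsistency stands and follows from the protocol's own thresholds. If 480 msec is the recovery limit, every baseline below 380 msec has a range of QTc values, from baseline plus 100 up to 479, that are both prolonged and recovered. Under the Section 7.1.7 table the range of baselines extends to below 420 msec. If recovery means return to baseline, the overlap disappears, but the same patient faces a longer hold and possible withdrawal.

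The number of patients affected is probably small: well under one on the rough count for Section 7.1.2, and more if sites work from the table. That count rests on assumed distributions and an inferred denominator. The 12 cases may include patients outside Part A, and that study's definition of confirmed prolongation is not given. The overlap itself needs none of these assumptions.

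The point is worth correcting because it concerns a known safety signal and the correction is cheap. It is no threat to the dose-finding result.

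**What to change.** Reconcile Sections 7.1.2, 7.1.3 and 7.1.7, and the flowchart, in four respects:
- No single QTc value should satisfy both the prolongation definition and the recovery condition.
- State one restart criterion in identical terms in the monitoring, restart and three-week sentences and in the table, including how 480 msec or baseline is to be read.
- Say whether a value that persists unchanged through the hold and restart counts as a recurrence.
- Make the 60 msec row of the table agree with Section 7.1.2 on the 480 msec floor.

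The sponsor's safety lead sets the limits; this review proposes none.

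The cost is wording in two sections, one table and possibly a figure. No extra ECGs are needed to establish baseline, because Section 10 already requires at least three. Depending on the criterion chosen, a few holds may become longer. The Alert Page already carries a clarification of this kind for potassium. Accrual closed in May 2010, so the practical use is for patients still on treatment and for classifying QTc holds, reductions and discontinuations consistently in the report.
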